**Recruitment**

For the purpose of eligibility assessment, the researcher will approach all Arabic schools in Klang Valley in Malaysia and invite these schools through formal invitation letters issued by the researcher’s university.

After getting the permission from responsible authorities of all Arabic schools (Appendix C), short online meeting will be arranged for each school. During the meeting, the researcher will explain the objectives and benefits of the study as well as the inclusion and exclusion criteria to the participants. Then a written consent will be sent to students and their parents. The students who agree to participate will be asked to answer the baseline data questionnaires (screening for eligibility). After the life skill educational intervention will be delivered to the intervention group, post-intervention assessment questionnaire will be distributed two times, immediately after the intervention completed and 3-month post-intervention for those who are eligible in screening stage.

**Randomization and Concealment Allocation**

The schools will be allocated randomly to intervention and control groups by using block randomisation after cluster size will be identified. To ensure allocation concealment, the allocation sequence of the selected schools will be assigned to a control group and an intervention group by the ratio 1 to 1 using random block sizes of 2 and 4 by an independent statistician from Universiti Putra Malaysia. To ensure allocation concealment, each cluster will receive a randomly generated treatment allocation unique code within serially numbered sealed opaque envelope. Then the research assistant will distribute the sealed opaque envelopes to the schools and the envelopes will be opened later and assigned the clusters according to their unique codes to the intervention or the control group based on the list codes generated by the software. Then the students will be assigned to the intervention group and to the control group.

***-* Research tools/instruments (state the validity/reliability/ scoring method)**

The questionnaires consist of four parts which are socio-demographic questionnaires, Depression, Anxiety, Stress Scale (DASS21), General Self-Efficacy Scale (GES), and Brief COPE scale (Appendix G). The first two parts of the questionnaires (socio-demographic and DASS21) will be sent to all students for screening purposes. The next 2 parts (GES and Brief Cope Scale) will be only filled by participants that reported mild to extra severe score of depression, anxiety or stress based on part 1.

**8- Intervention**

The interventional program's objectives will be to enhance the mental health, self-efficacy and coping mechanisms of Arabic adolescents at Arabic schools in Klang Valley in Malaysia.

**Development of the Intervention**

In this study, the educational intervention will be guided theoretically by the socio-cognitive theory. By consulting experts in this field, it will be developed based on the WHO Life Skills Education Program and UNICEF guidelines for implementing life skills.

The modules will be based on the research objectives, the target population, Arabic culture and the duration of the study, and the results of the pilot study and under the supervision of supervisory committee. The intervention will be intended to enhance the mental health and try to help participants to decrease depression, anxiety and stress, increase self-efficacy and the coping skills. This program will be also designed to improve participants’ ability to cope with the life’s challenges during migration and after settlement in the new country. some of the important considerations will be taken during developing and designing the preliminary activities, as they will be directly designed to focus on the coping with external stressors and emotions.

***-* Data collection (state the method, ensure privacy and confidentiality, quality assurance)**

At baseline before conducting the Life skill education program, questionnaires include (socio-demographic, Depression, anxiety and stress scale DASS-21, self-efficacy, and Brief Cope Scale) will be distributed to both intervention and control groups. The follow-up evaluation will be carried out immediately, and three months after the educational intervention for all students in the intervention group and the control group. The only exception being the questions on socio-demographics will be excluded for post-tests evaluation.

Data will be held in a confidential and anonymous manner ***and no third party “will have access or visibility to your data. This will be used for research purposes only***

9- **Study flowchart (diagrammatic illustration)**

Diagrammatic illustration of the study framework which provides a context to explain the study finding

[figure not shown]

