**4. Introduction**

**Background of the study**

Mental health is an essential element for the well-being of all individuals, families, and societies. It is fundamental to the population's health, quality of life and social and economic stability (Moksnes & Reidunsdatter, 2019). World Health Organization (WHO) has defined mental health as "a state of well-being in which the individual realizes his or her own abilities, can cope with the normal stresses of life, can work productively and fruitfully, and is able to contribute to his or her community” (Srivastava, 2011; Galderisi et al., 2017).

Children and adolescents' mental health are a global public health issue widely recognised as a critical component of research and government intervention (Barker et al., 2019). Worldwide, it is estimated that between 10% and 20% of children and adolescents suffer from mental health problems (Barker et al., 2019; Teresa Gutmann et al., 2019).

Mental health conditions account for sixteen per cent of the global burden of disease and injury in people aged between ten to nineteen years (WHO, 2018). Half of adult mental health conditions arise in the middle of Adolescence, while three-quarters of them occurring by the middle of their twenties (WHO, 2019).

Depression and anxiety are the most frequently encountered mental health problems, which significantly impact children and adolescents. These disorders have been shown to increase the risk of adverse outcomes such as impairment, loss of productivity and community involvement, decreased educational performance, increased likelihood of engaging in risky behaviours, disability, and increased self-harm and suicide rates (Dray et al., 2015). Worldwide, depression is the fourth leading cause of illness and disability among adolescents aged 15-19 years and fifteenth for those aged 10-14 years. Meanwhile, anxiety is the ninth leading cause among 15-19 years old adolescents and sixth for those aged 10-14 years old (WOH, 2018).

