**Significance of the Study:**

Promoting and improving mental and emotional health is critical especially when considering migrant children and adolescents as they are part of the society and they will eventually become adults, they can engage with healthy lifestyles and reduce the burden of diseases and empower the abilities to succeed in adulthood.

This study can help Arabic students to reduce screening barriers apart from bridging the gap due to limited access to information and service for Arabic adolescents. This study also may contribute to the credibility of the effectiveness of utilizing a life skills education intervention in educating Arabic secondary school students about mental health and how to cope with daily stressors.

This research will directly benefit the students, their families, and friends, as well as to provide information to the researchers and health care workers who strive to produce beneficial interventions for adolescent migrants. Our finding also will benefit many organisations and high authorities such as Arabic embassies and Arabic school administrators, and the ministry of health and education of Arabic countries to improve mental health among Arabic children and adolescents. We expect that the interventions will promote mental health and empower teenagers with the essential life skills resources to reach the desired ability and overcome challenges.

Consequently, implementation of such programs for adolescent mental health can facilitate the development of adolescent mental health services delivered through the existing health and social services. Promote coordinated inter-sectoral action for positive mental health and prevention of mental disorders, so this will establish linkages between education and health services to enable early recognition and management of any mental, neurological and substance use disorders. Facilitate the strengthening of health systems and promote monitoring, evaluation and research.

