**The inclusion criteria for students:**

(1) Arabic Students aged from 14 to 18 years old.

(2) students who give the assent from them and consent from their parents.

(3) student who have scored mild to extremely severe score in depression, anxiety and stress based on baseline assessment.

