**The exclusion criteria for students:**

(1) students who refuse to participate.

(2) Students who have hearing limitations, because they cannot interact during the online session.

(3) Students who have diagnosed or treated of mental health problems before based on their school file, because it may interfere with the effect of the program.

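### The confidentiality rule under Data collection has no safety exception; read literally, it bars passing an extremely severe DASS-21 score to an outside service

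*Protocol*

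**What the plan says.** The confidentiality rule stands in the Protocol under Data collection. It opens with "Data will be held in a confidential and anonymous manner" and continues that no third party "will have access or visibility to your data. This will be used for research purposes only". No exception is attached there, and none appears in any other section available for review.

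The other provisions that bear on it are these:

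- **Inclusion criteria for students:** ages 14 to 18, and "student who have scored mild to extremely severe score in depression, anxiety and stress based on baseline assessment".
- **Exclusion criteria for students:** "Students who have diagnosed or treated of mental health problems before based on their school file".
- **Research tools/instruments:** the DASS-21 goes to all students as the screen, and the self-efficacy and coping scales "will be only filled by participants that reported mild to extra severe score of depression, anxiety or stress".
- **Recruitment:** both later assessments go only to students found eligible at screening.
- **Data collection:** after baseline, follow-up takes place immediately and "three months after the educational intervention for all students in the intervention group and the control group".
- **Background of the study:** the adverse outcomes listed for depression and anxiety include "disability, and increased self-harm and suicide rates".
- **Significance of the Study:** "This study can help Arabic students to reduce screening barriers apart from bridging the gap due to limited access to information and service".

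**The concern.** The trial looks for symptomatic minors and will find them. Because students with a recorded diagnosis or treatment are excluded, a very high DASS-21 score may be the first sign anyone has of a problem. The people who see that score have one written rule on what they may do with it, and the rule sets two limits: who may see the data and what the data may be used for. A referral to an outside service falls foul of both.

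What is at stake is participant safety. A member of staff who follows the sentence as written would hold an extremely severe score in a 14-year-old and have no stated permission to pass it to a service. This applies equally in the control arm, which is screened and followed under the same rule but is not given the programme.

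**Working it through.** No sample-size, power or error-rate arithmetic applies. The check sets the provisions side by side and asks what the rule permits.

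**1. Does the trial select students to whom this could matter?** Yes. The inclusion criterion runs up to the extremely severe band in 14-18-year-olds. The exclusion criterion removes those already known from the school file.

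**2. Does the team know the score?** Yes. The DASS-21 band decides who is given the remaining scales (Research tools/instruments) and who receives the two later assessments (Recruitment). The result is acted on student by student.

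**3. What does the rule allow, taken literally?** Test each possible recipient against the two limits.

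| Recipient of the score | Third-party limit | Research-only limit |
|---|---|---|
| The student | Not engaged: the student is the participant | Advising the student releases the data to nobody else |
| Parent | Open: 'third party' is not defined, and parents give consent | A safety disclosure is not a research use |
| School | Open: the school gives permission and its files are used for eligibility | A safety disclosure is not a research use |
| Health or counselling service | Barred on an ordinary reading | A safety disclosure is not a research use |

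Only the last row fails both limits clearly. For parents and schools the first limit is uncertain and the second still restricts use. For the student the rule is no obstacle.

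**4. Does another section lift the rule?** None that is available does. The sections on sampling, recruitment, randomisation, instruments, intervention, data analysis and expected outcomes contain no step for notifying anyone of a severe score. The consent pages, the appendices and the study flowchart could not be seen.

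**5. How far does the rule reach?**

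- Assessments: 1 baseline + 2 follow-ups = 3 per enrolled student.
- Schools: 6 intervention + 6 control = 12.
- Time from first to last assessment: at least 3 months plus the length of the programme, which is not stated.
- Number of students scoring extremely severe: not estimable, because the protocol gives no expected distribution of DASS-21 bands.

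**6. Is 'anonymous' accurate?** No. The school-file check needs a named student. Follow-up restricted to screen-eligible students needs a contact. The GEE on three repeated measures (Data analysis) needs each student's records linked over time. The data are coded, not anonymous. This is a clerical correction and adds nothing to the weight of the main point.

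**The case against.** The best answer is that this reads too much into a privacy sentence. Its wording addresses the participant directly and contains a stray quotation mark, as though lifted from an information sheet. Research-only use is a common assurance against secondary use, and nothing in it tells staff to withhold a safety concern. Limits to confidentiality for minors would naturally sit in the consent and assent documents, and a short general statement with a detailed exception elsewhere need not be a contradiction. A promise of privacy also has value here: the DASS-21 is both the screen and the source of the primary outcome, so candour matters.

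Much of this stands, and it rules out three stronger readings that a reader might infer:

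- *That the trial has no referral procedure.* The documents do not support this. The places where one would most likely be found were not available.
- *That the rule leaves staff unable to act at all.* It does not. They may advise the student, and parents and schools may fall outside an undefined term.
- *That the rule breaks a commitment made under Significance of the Study.* That section describes hoped-for benefits, and its link between education and health services is said to follow from implementing such programmes. It does not promise to refer individual participants. There is a tension of purpose and nothing more.

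The objection does not remove the wording itself. However it came to be there, it is the only confidentiality rule shown, it is unqualified, and on its face it excludes an outside service on both limits. If an exception does exist elsewhere, the sentence should at least point to it.

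**Conclusion.** The point holds as a badly fixed rule and should be corrected before screening starts. Read literally, the Data collection sentence bars passing an extremely severe DASS-21 score to a health or counselling service for safety. The trial selects symptomatic adolescents without a recorded diagnosis or treatment, and its team knows each student's screening band.

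The conclusion rests on two assumptions: that the sentence is applied as written, and that an outside service is a third party in the ordinary sense. Confidence is medium, because an exception may exist in unseen material. The rule applies to every assessment in both arms, but how many students it would affect is unknown. No effect on alpha, power, sample size or precision is claimed.

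**What to change.** Keep the sentence and add an exception at its end:

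*except where disclosure to a parent or an appropriate service is needed for the participant's safety, including any DASS-21 score in the extremely severe band (or another trigger agreed with the ethics committee) at any of the three assessments in either arm.*

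Naming the band gives staff a default to act on, while the ethics committee can still set a different trigger. Align the consent and assent wording before the first DASS-21 screen, so that students and parents know the limit before they answer. If those documents already contain an exception, make the two texts agree. In the same edit, change 'anonymous' to 'coded'.

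The cost is a wording change to the protocol, consent and assent. The downside is a less absolute privacy promise, which may slightly reduce consent or candour on the DASS-21. Using the same wording and trigger in both arms keeps the procedure even-handed.

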**10.** **Data analysis**

We will use SPSS Statistics version 25.0 (IBM Corp) to analyse the data. Statistical significance will be considered as a P value of less than .05. Analysis of the data will take into account clustering of students within schools. The study will use statistical analyses, including:

Descriptive analyses using the mean and standard deviation for continuous variables and the count and percentages for the dichotomous or categorical variables will be used to describe the data at baseline. Descriptive statistics of the respondents’ socio-demographic characteristics, chi-square test for nonparametric categorical variables, and the Mann-Whitney-U test was used for comparison of continuous and not normally distributed data, and 2-tailed t test for continuous variables, to compare between the control and intervention groups on socio-demographic variables and primary and secondary outcome measures. In relation to the missing data, the intention-to-treat (ITT) analysis will be used.

The effectiveness of the intervention will be assessed using the generalized estimation equation (GEE). Specifically, the differences in the research hypothesis in terms of student’s depression, anxiety and stress levels will be compared at 3 points—time 1 (pre-intervention), time 2 (immediately post-intervention), and time 3 (3-month follow-up) between and within the intervention and the control groups adjusted for covariate variables.

The GEE method will be chosen because of its efficiency in appropriately modelling the structure of the correlations of the pre-post repeated measures and its low degree of reliance on the assumption of normality in the distributions of data for the variables in the analysis. Furthermore, in the context of RCT research, multilevel models such as the GEE are the most appropriate model because they permit the estimation of treatment effects (i.e., group differences) across multiple time points within a single statistical model (Wears, 2002; Huh et al., 2012).

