**7. Research methodology**

- **Research design**

This study is quantitative in nature and experimental in design. Specifically, this is a parallel cluster‐randomized controlled trial (cRCT). The schools will be the unit of randomization (clusters). The trial will be used to assess the effectiveness of online life skills program in reducing mental health problems (depression, anxiety and stress) among Arabic adolescents in Klang Valley, Malaysia. There are around 18 well‐known Arabic schools in Klang Valley area, with students from different Arab countries (i.e., Yemen, Iraq, Egypt, Libya, Syrian, Saudi Arabia, and etc).

- **Study location (state and justify the exact study location)**

The study will be located in Klang Valley, in the state of Selangor, Malaysia.

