***-* Sample size estimation (to consider non-response or attrition rate)**

**Sampling size**:

The total sample size needed will be calculated by applying the formula for two population means

Means and standard deviation used for the intervention group and control group are based on the estimation offered in a previous RCT (Osborn et al., 2020). Calculation of the required sample size in this study was performed based on the guidelines in the CONSORT for cluster RCTs. By considering the account intra-class correlation coefficient (ICC), it is necessary to multiply the sample size in RCTs by design effect=1+(m–1)*ICC, where m is the average cluster size. The formula for fixed number of clusters with unequal cluster sizes will be used. Adequate sample size after Adjust for attrition rate and expected proportion eligible and multiply with design effect= 165. Therefore, the total sample size required was 165 students. Number of clusters (schools) = estimated sample size/ cluster size = 165/54=3. Following the sample size calculation, the number of schools needed will be 3 schools. However, in order to get the required sample size, a total number of 12 schools that met the inclusion and exclusion criteria during the study time will be included in the study.

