***-* Sampling method and subject recruitment**

**Sampling Method**

A cluster sampling will be used for selection of the schools. There are 12 Arabic schools in Klang Valley that meet the inclusion and exclusion criteria for this study and they will be selected to be included in the study. In order to get the required sample size, the total number of 12 schools that met the inclusion and exclusion criteria during the study time will be included in the study. Each of the schools (clusters) will then receive a serially numbered unique code. The clusters will be assigned to the intervention or control group by the ratio 1 to 1 and will be performed using block randomization using random block sizes of 2 and 4 by an independent statistician from Universiti Putra Malaysia. Therefore, 6 clusters will be in the intervention group and 6 clusters will be in the control group. Then all the students (aged 14-18 years) in the selected school, and who give assent and consent from their parents to participate will be included in the study.

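### Section 10 promises to allow for clustering by school, yet names ordinary two-sample tests for the outcomes and explicitly names no school-adjusted analysis of self-efficacy and coping

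*Protocol*

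**What the plan says.** On the design, Section 7 states: "The schools will be the unit of randomization (clusters". The sampling method adds that "6 clusters will be in the intervention group and 6 clusters will be in the control group".

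Section 10 (Data analysis) makes four statements that bear on this point:

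- Near the start it gives a general undertaking that the grouping of students in schools will be allowed for.
- After a sentence on describing baseline data, it names the chi-square test, the Mann-Whitney U test and the two-tailed t test "to compare between the control and intervention groups on socio-demographic variables and primary and secondary outcome measures". No time point is attached, and no cluster-adjusted form of these tests is named.
- It assigns the assessment of effectiveness to a GEE, and then narrows this: "Specifically, the differences in the research hypothesis in terms of student’s depression, anxiety and stress levels will be compared at 3 points". The reason given for the GEE is that it models the correlation of repeated measures. School is not mentioned there.
- The threshold is common to all of this: "Statistical significance will be considered as a P value of less than .05".

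Self-efficacy and coping are the secondary outcomes in Section 11. The research question in Section 5 includes them in the comparison between and within arms at both follow-up times, with covariate adjustment.

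**The concern.** In their usual form the three named tests treat every student as an independent observation. When whole schools are allocated, students in one school share an allocation and tend to resemble each other. The standard error from such a test is then too small and its p-value too low. That conflicts with the undertaking on clustering in the same section.

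The exposure is greatest for self-efficacy and coping. An analyst who followed only the methods explicitly tied to named outcomes would fit a GEE to depression, anxiety and stress and would compare the arms on the secondary outcomes with tests that ignore school. Claims of benefit on those outcomes could then rest on overstated significance. The GEE itself could be fitted with only the student as the repeated-measures unit, because nothing in its description says how school enters.

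**Working it through.** **The plan's own figure.** "Number of clusters (schools) = estimated sample size/ cluster size = 165/54=3". The division gives 165/54 = 3.06, which rounds to 3 as stated. The total ("Therefore, the total sample size required was 165 students") cannot be rebuilt, because the protocol gives no means, standard deviation, power, ICC, attrition or eligible proportion. The point does not depend on rebuilding it.

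**Inputs.**

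- 12 schools, 6 per arm (Sampling Method).
- 165 students (Sampling size), so m = 165/12 = 13.75 per school.
- Two-sided nominal level 0.05 (Section 10).
- Variance inflation by the protocol's own formula: "multiply the sample size in RCTs by design effect=1+(m–1)*ICC, where m is the average cluster size".
- ICC: not given in the protocol. The range 0.01 to 0.10 is an assumption.

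**Formula.** With design effect DE = 1 + (m − 1) × ICC, an unadjusted test rejects under the null with probability 2 × [1 − Φ(1.96/√DE)].

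**Example at ICC 0.05.** DE = 1 + 12.75 × 0.05 = 1.6375, √DE = 1.280 and 1.96/1.280 = 1.53. The two-sided tail area is 12.6%.

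**Results, with a simulation check.** The simulation used 6 against 6 equal schools of 14 students and 4,000 runs per setting.

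| Assumed ICC | DE at 13.75 | Type I error, formula | Simulated t test | Simulated Mann-Whitney U |
|---|---|---|---|---|
| 0.01 | 1.1275 | 6.5% | 6.2% | 6.2% |
| 0.02 | 1.2550 | 8.0% | 8.3% | 8.3% |
| 0.05 | 1.6375 | 12.6% | 13.5% | 12.9% |
| 0.10 | 2.2750 | 19.4% | 19.5% | 19.1% |

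At ICC 0 the simulated t test rejected in 4.7% of runs, so the excess comes from clustering. In the same simulations a t test on the 12 school means (10 degrees of freedom) rejected in 4.7% to 5.2% of runs at every ICC.

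**Which outcome is explicitly covered by which method.**

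| Outcome | Two-sample tests | GEE |
|---|---|---|
| Depression, anxiety, stress | Yes, as primary outcomes | Yes, by name |
| Self-efficacy, coping | Yes, as secondary outcomes | Not named; possibly meant by the general sentence |

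**Two readings of the test sentence.**

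- *Outcome comparison.* The error rates above apply directly to claims about the intervention.
- *Baseline only.* The same inflation applies to the baseline p-values. The sentence then supplies no effectiveness analysis for self-efficacy and coping, and no other sentence in Section 10 names them.

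**The case against.** The strongest reply is that the test sentence concerns baseline. It follows a sentence about baseline description and groups the outcomes with socio-demographic variables, which the data collection section says are not asked again after baseline. All the outcome scales are also collected at baseline. Effectiveness is then handed to the GEE in a separate paragraph, in general terms. The research question wants an adjusted comparison of self-efficacy and coping over time, and of the named methods only the GEE fits that. This stands as a plausible account of intent. It does not settle the matter, because the sentence carries no time point, and on this reading the baseline p-values still ignore school.

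A second reply is that the general undertaking on clustering governs everything after it, and that a full list of models by outcome may sit in an analysis plan that is not shown. This also stands in part: the fault is an unresolved contradiction in stated text, not a declared intention to ignore clustering.

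A reader might infer more than the documents support:

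- *That the primary comparison rests on naive tests.* It does not; the primary outcomes have a GEE.
- *That self-efficacy and coping have no other analysis at all.* This is true only of what is explicitly named.
- *That the error reaches 11.3%, 30.5% or 43.5%, the values at 54 students per school for ICC 0.01, 0.05 and 0.10.* The 54 belongs to the three-school calculation. With 12 schools it would mean 12 × 54 = 648 students, against a stated 165.
- *That baseline tests are pointless because their null hypothesis is true by design.* The sampling method can be read as bringing students in after schools are allocated, so selective recruitment could create real differences.
- *That baseline tests will choose the covariates.* Nothing in Section 10 links the two.

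**Conclusion.** The point holds in a limited form. Section 10 contradicts itself: it undertakes to allow for clustering, then names tests that do not in their ordinary form, applies them to primary and secondary outcomes, and leaves self-efficacy and coping out of the GEE text. Correction is needed whether the tests are meant for follow-up or for baseline.

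If the tests are used on outcomes, the actual type I error of a nominal 5% test is about 6.5% to 19.4% for ICCs of 0.01 to 0.10. This rests on the assumed ICC range, on 165 students spread evenly over 12 schools, and on a normal approximation that the simulation supports. The error exceeds 5% at any positive ICC and would be higher if more students per school were enrolled. The text does not establish that these tests will be used at follow-up, so the figures show what the wording permits, not what will certainly happen.

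**What to change.** Amend Section 10 in three places:

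1. Restrict the two-sample comparison to a description of baseline by arm (means and standard deviations, counts and percentages), with no p-value from a test that ignores school.
2. State that the GEE covers self-efficacy and coping as well as depression, anxiety and stress, at the same three time points.
3. State that all between-arm inference treats school as the cluster, with a small-sample correction suited to 12 clusters, and name that correction.

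The cost is a short text change, a model run for two further outcomes, and slightly wider confidence intervals than tests that ignore school would give. No data collection changes.
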